## Abstract

**Background:**

Healthcare systems are not well designed to help people maintain or improve their health. They are generally not person-focused or well-coordinated. The objective of this study is to evaluate the effectiveness of the Health Teams Advancing Patient Experience: Strengthening Quality (Health TAPESTRY) approach in older adults. The overarching hypothesis is that using the Health TAPESTRY approach to achieve better integration of the health and social care systems into a person’s life that centers on meeting a person’s health goals and needs will result in optimal aging.

**Methods/design:**

This is a 12-month delayed intervention pragmatic randomized controlled trial. The study will be performed in Hamilton, Ontario, Canada in the two-site McMaster Family Health Team. Participants will include 316 patients who are 70 years of age or older. Participants will be randomized to the Health TAPESTRY approach or control group. The Health TAPESTRY approach includes intentional, proactive conversations about a person’s life and health goals and health risks and then initiation of congruent tailored interventions that support achievement of those goals and addressing of risks through (1) trained volunteers visiting clients in their homes to serve as a link between the primary care team and the client; (2) the use of novel technology including a personal health record from the home to link directly with the primary healthcare team; and (3) improved processes for connections, system navigation, and care delivery among interprofessional primary care teams, community service providers, and informal caregivers. The primary outcome will be the goal attainment scaling score. Secondary outcomes include self-efficacy for managing chronic disease, quality of life, the participant perspective on their own aging, social support, access to health services, comprehensiveness of care, patient empowerment, patient-centeredness, caregiver strain, satisfaction with care, healthcare resource utilization, and cost-effectiveness. Implementation processes will also be evaluated. The main comparative analysis will take place at 6 months.

**Discussion:**

Evidence of the individual elements of the Health TAPESTRY platform has been shown in isolation in the previous research. However, this study will better understand how to best integrate them to maximize the system’s transformation of person-focused, primary care for older adults.

**Trial registration:**

ClinicalTrials.gov NCT02283723

**Electronic supplementary material:**

The online version of this article (doi:10.1186/s13012-016-0407-5) contains supplementary material, which is available to authorized users.

## Background

Healthcare systems are not well designed to help people maintain or improve their health. They are generally not well-coordinated and plagued with barriers to a person-focused care system [1, 2]. In Canada, current provincial healthcare systems are confronted with working to overcome disorganized connections among primary, secondary, and community care [3] and the use of processes that are reactive versus proactive [4]. Further, the current system is challenged by the burden of provider-patient interactions focused on a single disease rather than approaches that account for people who have multiple chronic conditions [4, 5]. Although the field of medicine has evolved over the years to focus on wellness versus illness, much change is still needed to take into account patient goals and preferences [6]. Finally, the system lacks coordinated strategies that address the social determinants of health [3, 7]. Transformational healthcare system change is needed if a person is to truly realize the World Health Organization’s (WHO) definition of health, “a resource for everyday life, not the objective of living; it is a positive concept, emphasizing social and personal resources, as well as physical capacities” [8].

Countries with a strong emphasis on primary healthcare have realized better health outcomes and health equity [9–11]. Effective primary healthcare is community-based, promotes healthy lifestyles as a pathway to disease prevention, provides ongoing care for chronic conditions, and recognizes the importance of the broad determinants of health [12]. Primary healthcare embraces a wide suite of services and involves a broad range of healthcare providers in a manner that is person-focused and coordinated [13]. It has been identified that integrated care allows a person to plan their care with people who work together to understand them and their caregivers, allow them control, and bring together services to achieve outcomes of importance to them [14]. A strong primary healthcare system also needs to be well integrated with the rest of the healthcare system. The WHO defines integrated care as the bringing together of inputs, delivery, management, and organization of services related to diagnosis, treatment, care, rehabilitation, and health promotion [15]. High-quality integration encompasses better care delivery horizontally through improved interdisciplinary team collaboration and vertically across different levels of care such as in the home, primary, secondary, and tertiary care [15]. Taking into account complexity theory concepts when considering effective healthcare delivery also recognizes that delivery of healthcare itself is a complex adaptive system and, as such, changes according to current demands [16, 17]. Therefore, improving primary healthcare requires the many components of the healthcare system to undergo whole-scale transformational system change and to do so in a manner that produces person-focused coordinated care.

Individuals ≥65 years are the fastest growing age group in Canada. This age segment in July 2015, for the first time ever, outnumbered people aged ≤15 years [18-21]. Worldwide, the number of people over the age of 60 is expected to double by 2050 [19, 20]. If no improvements are made to the current healthcare system, greater numbers of people will have unmet healthcare needs that will hinder healthy aging [20, 21]. Many older adults report being in excellent or very good health and are able to carry on daily activities on their own [22]; however, it is also well recognized that age is associated with increased numbers of chronic conditions [23], which can lead to functional decline and increased use of the healthcare system [19, 23, 24]. A well-functioning healthcare system will help keep people healthy and living at home and properly supported. Further, a person-focused approach has been proposed to tackle multimorbidity [25, 26].

### Theory and development approaches

The chronic care model was used to identify key themes and players that should be incorporated into the intervention [27]. Six core elements of the chronic care model were incorporated: healthcare organization and leadership, linkage to community resources, support of client self-management, coordinated delivery system design, clinical decision support, and clinical information systems [27] (see Table 1). A five-pronged approach has been used to develop the Health Teams Advancing Patient Experience: Strengthening Quality (Health TAPESTRY) platform: (1) developmental evaluation [28, 29], (2) participatory co-development [30, 31], (3) formal investigation of sustainability [32], (4) iterative pilot testing [30] including evaluation of implementation of the intervention, and (5) a pragmatic randomized controlled trial (RCT) to evaluate the effectiveness and cost-effectiveness. The combination of approaches allows the team to explicitly record and gain progressive insight into key decisions made during development including those intended to foster sustainability and scalability, ensure the views of key players were incorporated, and allow for improvements to the intervention to be made and tested in an iterative manner before large scale evaluation.

**Table 1 Tab1:** Chronic care model and health TAPESTRY

Element	Definition	Health TAPESTRY
Healthcare organization and leadership	Strong leadership, readiness for change, and effective incentives to systematically promote successful quality improvement interventions.	Health TAPESTRY creates time and space for clinic huddles to take place to discuss clients individually in an organically defined, interprofessional process through support from clinic leadership.
		Clinic leadership supports integration of volunteers into the team and the adoption and use of e-health technologies
Linkage to community resources	Efficient use of community resources such as peer-support groups, community programs, and counselling to improve the quality of care and support offered to patients and improve cost-effectiveness in the system.	Health TAPESTRY offers linkages to community organizations through support of volunteers and directed healthcare provider referral or connection based on goals and needs oriented action plans.
Support of patient self-management	Patient empowerment, activation, and support of self-management skills to effectively sustain management of chronic conditions.	Health TAPESTRY volunteers serve as advocates for clients and encourage self-management through follow-up and discussion of client-identified health goals. Healthcare providers encourage self-management activities through education and actions based on goals and needs oriented action plans.
Coordinated delivery system design	Disconnected care across multiple providers and caregivers is a point of inefficiency in the health system; therefore, addressing lack of coordination to significantly improve patient experience.	The KindredPHR seeks to allow clients to better connect to all their providers in a more coordinated way. The Health TAPESTRY specific applications generate information in the home that is shared electronically with the clinic.
Clinical decision support	Facilitating the use of evidence-based guidelines and patient assessment tools to enhance effectiveness.	The Health TAPESTRY App contains modules (surveys, risk algorithms) that have been supported by evidence and expert opinion.
Clinical information systems	Improving patient-provider and provider-provider communication, using reminder systems, documenting treatment plans and sending secure messages to enhance the delivery of proactive care.	The KindredPHR offers secure messaging between clients and providers and allows for establishment of reminders, tracking of health information and treatment plans, and recording data. Communication is also be facilitated by the clinic EMR.

*PHR* personal health record, *EMR* electronic medical record

### Evidence supporting the elements of Health TAPESTRY

Health TAPESTRY seeks to bring together elements of healthcare delivery into a combined platform that capitalizes on current system strengths yet moves these forward using an integrated healthcare approach. Specifically, Health TAPESTRY centers on meeting a person’s health goals with the support of trained community volunteers, technology, an interprofessional team, system navigation, and community engagement. Healthcare volunteers have been shown to provide social support that is both physically and emotionally therapeutic to patients [33, 34]. Secondly, a multitude of benefits have been report from electronic medical records (EMRs) [35–37]. Additionally, with some mixed evidence, patient on-line access to their own health information (through personal health records (PHR)) has been shown to improve patient self-care, health outcomes, and communication and engagement with clinicians [38, 39]. Thirdly, much evidence supports the positive impact of team-based care on numerous health outcomes across several chronic diseases [40–42]. Finally, system navigation has been associated with important health outcomes [43, 44] and helps to address social determinants of health [45, 46].

We are unaware of any studies that integrate the components of Health TAPESTRY into a coordinated approach intended to improve delivery of primary healthcare. In essence, Health TAPESTRY is a health and social care approach that centers on meeting a person’s health goals and health needs explicitly gathered with the support of technology, community volunteers, an interprofessional team, and system navigation and better links between primary care and community organizations. It is a complex, multilevel approach to integration, from both system level and individual level perspectives.

The overarching aim of the Health TAPESTRY platform is to promote optimal aging. Health TAPESTRY intends to promote optimal aging through (1) intentional, proactive conversations about a person’s life and health goals and health risks and then initiation of an action plan that supports achievement of those goals and addressing of health risks; (2) improved collaborative working within the interprofessional primary care team, community service providers, and informal caregivers; (3) training volunteers to serve as a link between the person in their home and their primary care team; and (4) using technology including the PHR that allows personal health information and patient health goals to link directly to the EMR with the primary healthcare team.

### Overall objective, research questions, and hypothesis

We aim to evaluate the implementation and effectiveness of the Health TAPESTRY approach in older adults. The primary research question is, what is the effectiveness of the Health TAPESTRY approach on the identification and attainment of a person’s health goals in older adult participants compared to people not receiving the Health TAPESTRY approach? Our hypothesis is that better integration of the health and social care systems into a person’s life will allow a person to better attain their health goals. Four secondary research questions will also be asked with respect to several participant outcomes, cost-effectiveness, sub-analyses, and intervention duration (see Additional file 1 for a complete list of secondary research questions). An additional set of questions will be asked related to the processes of implementation of each component of the Health TAPESTRY approach (see Additional file 1).

## Methods/design

### Design

This is an unblinded delayed intervention pragmatic RCT. Participants in the control group will receive the intervention at 6 months, and both groups will continue to be part of the study until the 12-month mark (Fig. 1). The main analysis will be group comparisons at 6 months. Both groups will be also assessed at 12 months. Ethics approval was granted from the Hamilton Integrated Research Ethics Board (8 December 2014). The trial has been reregistered with Clinical Trials.gov NCT02283723. We used the SPIRIT guidelines to guide reporting of our trial protocol [47].

**Fig. 1 Fig1:**

Study design. *R* randomization, *T*
_*0*_ baseline, *T*
_*6*_ 6-month time point, *T*
_*12*_ 12-month time point

### Trial setting

The study will be performed in Hamilton, Ontario, Canada, at the McMaster Family Health Team (MFHT) and surrounding communities. The MFHT consists of groups of family physicians and other healthcare professionals, providing 7-day-a-week access to care, supported by an EMR, and providing a broad collection of services based on community needs. The MFHT is paid using a blended model of funding, including capitation and fee for services, bonuses for achieving prevention targets, and special payments to expand the scope of care [48]. The MFHT has approximately 32,000 rostered patients, 36 family physicians, 74 medical residents, 15 locums, 18 nurses, and 26 allied healthcare professionals.

### Study participants

As a planned pragmatic RCT, efforts will be made to limit the restrictiveness of the trial inclusion criteria. Inclusion criteria included patients rostered with MFHT, aged 70 years or older, and living in Hamilton, Ancaster, Dundas, Stoney Creek, Grimsby, Caledonia, or Rockton, Ontario. Exclusion criteria included people who reside in long-term care, will be out of the country for more than 50 % of trial duration, are palliative or receiving end-of-life care, or do not speak English or have a family member who speaks English. An initial list of potential participants will be generated through a query using the clinical EMR. Family physicians will screen lists of possible participants for exclusion criteria, and then invitation letters will be sent to all remaining participants. All volunteers and healthcare team members who are involved in the study will be invited to participate to provide their perspective as part of the implementation evaluation.

### Randomization and blinding

While it is recognized that there could be potential contamination between intervention and control groups by the primary care providers who will have participants in both arms, the intervention focuses on identifying a person’s health goals which a salient component to all other actions to take place as part of the intervention. Thus, without the processes in place to receive information about a person’s goals, contamination is unlikely, and so it was felt that clustering at the level of the practice was not necessary.

The randomization process will involve an automated central (allocation concealed) computerized randomization sequence, with the patient as the unit of randomization. Randomization will be stratified by participant gender and MFHT site (McMaster Family Practice or Stonechurch Family Health Centre). Couples will be accepted into the study to encourage study participation and to ensure equitable access to the intervention. Recognizing the potential influence of one member of a couple on the other, both members will be randomized into the same group. One member of the couple will be randomly selected to contribute their data to the main analysis.

Participants, caregivers, and volunteers will not be blinded; however, there will be some masking of groups: participants will not explicitly be told that they are in the initial or delayed group. Physicians and other members of the healthcare team will be not be formally blinded to allocation; however, there will be some masking as they will only know a participant is receiving the intervention once a Health TAPESTRY report is reviewed and may not recognize whether a person has been allocated to the intervention or control group. Data analysts will be blinded to the study group.

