### Outcomes

Tables 2 and 3 summarize the measures, timing, and data collection method used for the primary and secondary outcomes, in addition to the measures and timing of the implementation processes. The following section gives more detail for clarity and is broken down into two broad sub-sections: client outcome measures and implementation processes. A description of the tracking of adverse events and the economic analysis is also included.

**Table 2 Tab2:** Summary of trial client outcomes and implementation processes

Client outcomes				
Variable/outcome	Hypothesis	Outcome measure	Timing	Methods of analysis^a^
Goal attainment	GAS score will be higher in the intervention arm compared to the control arm at 6-months; proportion of participants who report maintaining or improving in the top priority goal area will be higher in the intervention arm than the control arm at 6-months	Goal attainment scaling score [53] obtained from a structured interview; proportion of participants who report maintaining or improving in their top priority goal area	*T* _6_, *T* _12_	Linear regression for continuous variables; logistical regression for categorical variables
Self-efficacy	*Higher* self-efficacy, quality of life, optimal aging, social support, access, comprehensiveness, patient empowerment, patient-centeredness, and satisfaction of care and *lower* caregiver strain, hospital admissions, and emergency room visits will be reported in the intervention arm compared to the control arm at 6-months	Self-efficacy for managing chronic disease [55]; self-report	*T* _0_, *T* _6_, *T* _12_	
Quality of life		EQ5D-5L [56]; self-report	*T* _0_, *T* _6_, *T* _12_	
Optimal aging		Single-item optimal aging question from the Canadian Longitudinal Study on Aging [57]; self-report	*T* _0_, *T* _6_, *T* _12_	
Social support		DUKE social support index [58]; self-report	*T* _0_, *T* _6_, *T* _12_	
Access		CIHI common indicators; self-report [59]	*T* _0_, *T* _6_, *T* _12_	
Comprehensiveness of care			*T* _0_, *T* _6_, *T* _12_	
Patient empowerment			*T* _0_, *T* _6_, *T* _12_	
Patient-centeredness			*T* _0_, *T* _6_, *T* _12_	
Caregiver strain		4-item Zarit screen [60]; self-report	*T* _0_, *T* _6_, *T* _12_	
Satisfaction with care		Single item, satisfaction rated from 1 to 10; self-report	*T* _0_, *T* _6_, *T* _12_	
Hospitalizations and emergency room visits		EMR abstraction	*T* _0_, *T* _6_, *T* _12_	

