#### Client outcomes

We propose to test using two analysis sets: ITT set, considering all patients as randomized regardless of whether they received the intervention and a “per protocol” analysis set. A per protocol analysis will include all participants who received the intervention including both members of a couple assigned to the intervention group compared with all participants randomized to the control group including both members of a couple assigned to the control group.

Quantitative data analysis will include descriptive analyses with means and standard deviations calculated for the continuous variables and frequencies calculated for categorical variables. Data will be summarized in tabular or graphical form. The main between-group comparison will take place at 6 months. This point also serves as the control group’s baseline as they move into the intervention arm based on the delayed design. The comparison at 12 months then compares the effect of the intervention after 12 months of participation (original intervention group) versus 6 months of intervention (original control group).

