The analysis will be blind to study group allocation and will follow ITT principle. Dropouts will not be replaced. Reporting will follow the CONSORT extension for pragmatic randomization trials [66] and non-pharmacological interventions [67]. The baseline characteristics of the practices and patients will be reported by group as mean (standard deviation) or median (first quartile, third quartile) for continuous variables, depending on the distribution, and count (percent) for categorical variables. Multiple imputations will be used to handle missing data to enable ITT analysis. The data will be analyzed using generalized estimating equations—assuming exchangeable correlation structure adjusting for baseline scores, to analyze all outcomes [68]. The results will be reported as estimate of the effect, corresponding 95 % confidence interval and associated *p* values. All *p* values will be reported to three decimal places with those less than 0.001 reported as *p* < 0.001. The criterion for statistical significance will be set a priori at alpha = 0.05 and adjusted using the Bonferroni method for multiple secondary analyses. Analyses will be performed using SAS V9.4 (Cary, NC). There will be a single final analysis at the end of the trial. Subgroup analyses will include examining differences between the following groups: men and women; age less than 80 and 80+ years; those residing alone and residing with others; or those with three or more chronic conditions.

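### The per-protocol analysis keeps both members of each couple, but no stated model treats the couple as a cluster, so its standard errors may be somewhat too small

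*Protocol article*

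**What the plan says.** Under Randomization and blinding, the protocol article describes a sequence "with the patient as the unit of randomization", then makes an exception for couples: "Recognizing the potential influence of one member of a couple on the other, both members will be randomized into the same group". The next sentence limits the consequence for one analysis: "One member of the couple will be randomly selected to contribute their data to the main analysis".

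Under Data analysis, Client outcomes, two analysis sets are defined. The first is the "ITT set, considering all patients as randomized regardless of whether they received the intervention"; couples are not mentioned there. The second does mention them: "A per protocol analysis will include all participants who received the intervention including both members of a couple assigned to the intervention group". Its comparator is everyone randomized to control, again with both partners.

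Two models are stated. Table 2 (Outcomes) lists "Linear regression for continuous variables; logistical regression for categorical variables", and its footnote gives gender and clinic site as the adjustment variables. The Client outcomes text gives generalized estimating equations, "assuming exchangeable correlation structure adjusting for baseline scores, to analyze all outcomes". Neither place says what the cluster is.

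**The concern.** Because both partners always go to the same arm, a couple is in effect a randomized cluster of two. The protocol's stated reason for joint allocation, that partners may influence each other, is also a reason to expect correlated outcomes. Drawing one member removes that correlation from the main analysis. The per-protocol set puts both members back, and nothing stated for that set replaces the protection.

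With positively correlated partners in the same arm, a model that treats them as independent understates the standard error of the arm difference. Per-protocol intervals would be too narrow and the test would reject a true null too often. The per-protocol result could also look more precise than the main result partly because partners are counted as independent.

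**Working it through.** **Plan's own figure.** Power and sample size assumes SD 15, a difference of 5 GAS points, power 80% and alpha 0.05. A two-sided two-sample t-test gives 143 per arm, or 286 in total, as stated (284 by the normal approximation). The calculation treats participants as independent, which suits a main analysis with one member per couple.

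**Inputs not in the document.** The share of participants enrolled as couples, *f*, and the within-couple correlation, *r*, are not given. Both are assumed to lie between 0.1 and 0.5.

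**Variance inflation.** In an arm of *n* participants, *f·n*/2 pairs are correlated. The variance of the arm total is *n*σ² + 2·(*f·n*/2)·*r*σ² = *n*σ²(1 + *f·r*). With the same *f* in both arms, the variance of the arm difference is inflated by D = 1 + *f·r*.

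**Consequence of ignoring it.** The standard error is understated by 1 − 1/√D. The actual two-sided type I error is 2·[1 − Φ(1.96/√D)].

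| *f* | *r* | D | SE too small by | Type I error |
|---|---|---|---|---|
| 0.1 | 0.1 | 1.01 | 0.5% | 5.1% |
| 0.3 | 0.3 | 1.09 | 4.2% | 6.0% |
| 0.4 | 0.3 | 1.12 | 5.5% | 6.4% |
| 0.5 | 0.5 | 1.25 | 10.6% | 8.0% |

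**Simulation.**
- With 158 per arm and 20,000 runs, the independence analysis gave 6.1%, 6.3% and 7.9% for the last three rows.
- A second simulation used 286 participants, 96 of them in 48 couples (about 34%), *r* = 0.3 and 1,500 runs. Ordinary regression gave 6.7%, and an exchangeable GEE clustered on the couple gave 5.5%. The formula gives 6.2% for the former. With a Monte Carlo standard error of about 0.6 percentage points, the results agree with 6.2% and with the nominal 5%.

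**Apparent against real gain in precision.** Take *f* = *r* = 0.3 and ignore dropout and exclusions. One member per couple leaves 1 − 0.3/2 = 0.85 of the participants. Relative to that analysis, the standard error from keeping everyone appears to be √0.85 = 0.922 if partners are treated as independent. Correctly it is √(0.85 × 1.09) = 0.963. The apparent gain is about 7.8% and the real gain about 3.7%, so roughly half of it would be false.

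**The case against.** The strongest reply is that the plan may already handle this. A GEE with exchangeable correlation is a standard method for paired data. The Data analysis section presents Tables 2 and 3 as summaries and the text as the detail, so the GEE may be what governs. If its cluster is the couple, the per-protocol standard errors are sound. Naming a cluster variable is also something an article may leave to a fuller analysis plan.

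Part of this stands: the bias is conditional. Even so, the couple is not the obvious reading of the GEE. It is to be used for all outcomes, and in a main analysis with one member per couple every couple cluster has size one. The person measured at 6 and 12 months is an equally natural cluster, and that choice leaves partners independent. Nor is the point only missing detail, because the article itself fixes a set with both partners and, in Table 2, a model that ignores their correlation.

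A reader might go further and infer that both partners enter both analysis sets, so that the main analysis is affected too. The documents do not support this. Inclusion of both members is explicit only for the per-protocol set. The ITT phrase is conventional wording about analysing people regardless of treatment received, and the randomization section limits the main analysis to one member per couple. The two sit awkwardly together, but that is an ambiguity to reconcile.

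The upper end of the range needs half of all participants in couples and a correlation of 0.5, and nothing in the article supports either value.

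**Conclusion.** The point holds for the per-protocol analysis and is conditional. Its standard errors would be too small if within-couple correlation is positive and the model is either Table 2's regression or a GEE clustered on the person. Under the assumed ranges the effect runs from negligible to moderate: about 0.5% to 11% on the standard error, and about 5.1% to 8.0% for a nominal 5% two-sided test. It is not established that any standard error will be wrong, because the article leaves the GEE cluster open.

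Severity is low. The article ties the main 6-month comparison and the primary outcome to the ITT principle, so the primary conclusion does not rest on the affected set.

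**What to change.** This is a cheap improvement, made in three edits:

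1. In Client outcomes, state that in any analysis containing both members of a couple, including the per-protocol analysis, the couple is the GEE cluster and a single participant is a cluster of size one. Specify exchangeable working correlation and robust standard errors, and keep gender and site as covariates.
2. Align the methods column of Table 2 with the GEE in the text, so that one model is stated for each outcome.
3. Reconcile the ITT definition with the couple rule under Randomization and blinding by saying whether the ITT set holds one member per couple or both. If both, the clustering in the first edit applies there too.

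The cost is a few sentences and a couple identifier already known from randomization. The downside is slightly wider per-protocol intervals where partners are positively correlated.
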